**7.2 Safety Endpoints:**

- Vital signs (temperature, pulse, respiration, blood pressure);
- Laboratory tests: Complete blood count (WBC, RBC, HGB, PLT); Urinalysis (PRO, GLU, LEU, ERY); Liver function tests (AST, ALT, TBIL, γ-GT, ALP); Renal function tests (Scr, GFR); CK; TG; Coagulation profile (PT, APTT, TT, FIB);
- 12-lead ECG;
- AEs.

**8 Safety assessment**

**8.1 Definitions**

- AE: An AE is any unfavourable medical occurrence in a participant that may present as symptoms, signs, illness, or laboratory findings after taking the trial medication. These events are not necessarily causally related to the trial medication.
- SAE: A SAE is any adverse medical event that occurs after taking the trial medication and results in death, life-threatening situations, permanent or significant disability or incapacity, requires hospitalization or prolongation of existing hospital stay, or causes congenital anomalies or birth defects.
- Suspected Unexpected Serious Adverse Reaction (SUSAR): This refers to an adverse reaction that is both unexpected and serious, where the nature and severity of the clinical presentation exceed what is described in the drug's Investigator's Brochure, the marketed product's package insert, or the product characteristics summary, and where the reaction is not anticipated based on the current knowledge.
- Drug Adverse Reaction: This term refers to any harmful or undesired effect in clinical trials that is possibly related to the trial medication. There is at least a reasonable possibility of a causal relationship between the trial medication and the AE, meaning that the relationship cannot be ruled out.

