**8.2 Safety Information Related to the Trial Medication**

The trial drug, L-oxiracetam for injection, has been associated with clinical adverse reactions including anxiety, skin itching, rash, nausea, and stomach pain, which typically resolve after discontinuation of the drug. A few patients have reported psychiatric excitation and sleep disturbances.

The control drug, oxiracetam for injection, occasionally causes skin itching, nausea, psychiatric excitation, and sleep disturbances.

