8.7.2 Reporting of SAEs

Any SAEs occurring during the trial, whether related to the investigational drug or not, must be promptly treated by the researcher and immediately reported in writing to the sponsor, followed by a detailed written follow-up report. SAE reports and follow-up reports should use the subject's identification code from the clinical trial, not the subject's real name, national ID number, or address.

Upon receiving any safety-related information from any source, the sponsor must immediately analyze and assess it, including the severity, relationship to the investigational drug, and whether it was an expected event. The sponsor should promptly report any suspected and unexpected serious adverse reactions to all investigators and clinical trial sites involved, as well as to ethics committees; the sponsor should also report these reactions to the drug regulatory authority and health authorities.

Researchers, upon receiving relevant safety information from the sponsor about the clinical trial, must promptly acknowledge and review it, consider adjusting treatment for the subject, if necessary, communicate with the subject at the earliest opportunity if needed, and report any suspected and unexpected serious adverse reactions provided by the sponsor to the ethics committee.

For reports involving death events, researchers should provide other required information to the sponsor and ethics committee, such as autopsy reports and final medical reports.

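### The SUSAR definition in 8.1 joins nature and severity with 'and', so a listed reaction that is worse only in severity may fall outside the sponsor's onward reporting

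*Protocol*

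**What the plan says.** The SUSAR entry in Protocol section 8.1 has three parts. It begins: "This refers to an adverse reaction that is both unexpected and serious". It then sets the comparison with the reference document: "where the nature and severity of the clinical presentation exceed what is described in the drug's Investigator's Brochure", with the package insert and the product characteristics summary as alternatives. It closes with "and where the reaction is not anticipated based on the current knowledge".

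Section 8.2 says that L-oxiracetam "has been associated with clinical adverse reactions including anxiety, skin itching, rash, nausea, and stomach pain, which typically resolve after discontinuation of the drug", and adds psychiatric excitation and sleep disturbances in a few patients.

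Section 8.7.2 sets out the reporting chain. Every SAE, whatever its cause, "must be promptly treated by the researcher and immediately reported in writing to the sponsor". The sponsor assesses the information, "including the severity, relationship to the investigational drug, and whether it was an expected event". The onward step follows: "The sponsor should promptly report any suspected and unexpected serious adverse reactions to all investigators and clinical trial sites involved". The same reactions also go to ethics committees and to the drug regulatory and health authorities.

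**The concern.** The definition in 8.1 decides which serious reactions leave the sponsor and reach everyone else. If nature and severity must each exceed the reference, a reaction whose type is already listed can never qualify through severity alone. A known type of reaction appearing in a much worse form is information that other sites would want.

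It matters more here because section 1.4 says L-oxiracetam has not been marketed anywhere and that its risks are judged by reference to oxiracetam. The trial plans 236 patients on L-oxiracetam (section 10) in 74 centres (section 3.1). A single centre is unlikely to see a pattern by itself, so the onward report is how the others learn of it.

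**Working it through.** No arithmetic applies. The check is to follow one type of case through the sections.

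**Conditions for a SUSAR in 8.1, taken literally**

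1. The event is an adverse reaction. Under 8.5, the categories definitely, probably and possibly related count.
2. It is serious.
3. Its nature exceeds the reference document.
4. Its severity exceeds the reference document.
5. It is not anticipated on current knowledge.

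**Other definitions.** No other section defines unexpectedness or uses 'or' between nature and severity. Section 8.7.2 asks the sponsor to judge whether an event was expected but supplies no test of its own, so that judgement falls back on 8.1.

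**Test cases.** All are serious and possibly drug-related. For illustration, assume that the reference lists rash and describes a limited form.

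| Case | Nature exceeds | Severity exceeds | Literal reading | Collective reading |
| --- | --- | --- | --- | --- |
| Reaction type not listed | yes | yes (no severity is described for it) | SUSAR | SUSAR |
| Rash, far more severe than described | no | yes | not a SUSAR | SUSAR |
| Rash, within the described severity | no | no | not a SUSAR | not a SUSAR |

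The collective reading treats nature and severity together as one described profile and asks whether the presentation goes beyond it.

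Only the middle row changes with the reading. The closing clause of 8.1 bears on the same row. If it is a separate condition, a reader can say that rash was anticipated, and the case fails a second time. If it only restates unexpectedness, it adds nothing.

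**Consequences for the middle row under 8.7.2**

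- Investigator to sponsor: an immediate written report is required under either reading.
- Sponsor's assessment of severity, relationship and expectedness: required under either reading.
- Sponsor's onward report to investigators, sites, ethics committees and authorities: required under the collective reading, not required under the literal one.

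**The case against.** The strongest reply is that the wording is loose rather than wrong. Nature and severity can be taken together as the described profile, and a severe rash where only a limited one is described then exceeds it. The closing clause may simply repeat the word unexpected. Both points stand, and they rule out saying that the protocol expressly excludes such events. They do not remove the problem, since two natural readings of one reporting rule lead to opposite actions.

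A reader might infer that these events receive no rapid reporting at all. The document does not support that. Every SAE goes to the sponsor immediately, 8.3.2 requires it to be tracked until it resolves, stabilises or is explained, for deaths 8.7.2 has researchers supply further information to the ethics committee as well, and 4.4 calls for prompt stopping if serious safety issues arise. Only the sponsor's onward report is at risk.

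A reader might also infer that all seven reaction types in 8.2 count as expected at any severity, or that the protocol describes them as mild. Neither follows. The comparison is with the Investigator's Brochure or a product document, not with 8.2, and the severity those documents describe is unknown here. Section 8.2 says that five of the reactions typically resolve after discontinuation but gives no grade. A serious form may also differ in nature from the listed term, and would then meet even the literal test.

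Finally, earlier experience gives no sign that such cases will be common: section 1.3.4.2 reports no SAEs among 52 participants in the phase I pharmacokinetic study, and section 1.3.4.3 reports no drug-related SAEs in the 200-subject phase II trial. This limits the likely number of cases but does not make the rule clear.

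**Conclusion.** The point holds as a defect of definition. On its literal reading, 8.1 leaves a listed reaction that exceeds the reference in severity alone outside the SUSAR category, and 8.7.2 makes that category the only trigger for the sponsor's onward report. On the collective reading such a reaction is included. The protocol does not say which reading applies.

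The size cannot be stated as a number. It depends on what the reference document lists and how severely, and on how often a listed reaction becomes serious; the protocol gives neither. No efficacy endpoint, sample size or analysis is affected. The conclusion rests on the protocol's own reporting chain, not on any outside definition, and it assumes that no separate safety procedure settles the meaning. It merits correction because the rule, followed literally, gives the weaker safety outcome and is easy to repair.

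**What to change.** In 8.1, state that a reaction is unexpected if either its nature or its severity goes beyond the reference document. Reword the closing clause so that it explains the term and does not add a condition. In 8.7.2, refer to that definition both where the sponsor judges expectedness and where the onward report is triggered, so that the two steps use one test.

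The cost is a short wording amendment with the approvals that section 18 requires, and possibly a few more onward reports. Design, sample size and analysis do not change.

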**8.2 Safety Information Related to the Trial Medication**

The trial drug, L-oxiracetam for injection, has been associated with clinical adverse reactions including anxiety, skin itching, rash, nausea, and stomach pain, which typically resolve after discontinuation of the drug. A few patients have reported psychiatric excitation and sleep disturbances.

The control drug, oxiracetam for injection, occasionally causes skin itching, nausea, psychiatric excitation, and sleep disturbances.

**8.3 Management and Documentation of** **Adverse Events**

8.3.1 Management of Adverse Events

- Inpatients

If an AE occurs during a subject's hospital stay, it should be handled according to the following procedure:

Upon detecting an AE in a subject, the attending or on-duty doctor should promptly inform the researcher. If necessary, symptomatic treatment may be initiated first. The research physician should preliminarily assess the severity and relation to the investigational drug and provide further handling advice:

- - General AE: Close monitoring of the event's outcome or corresponding symptomatic treatment may be conducted;
  - Significant AE: The research physician should immediately inform the principal investigator. Based on the subject's condition, treatment may be temporarily suspended, medication dosage adjusted, or targeted treatment measures taken. If necessary, the principal investigator may decide whether to urgently unblind (if applicable);
  - SAE: Handled and reported according to the following "8.7".
  - The research physician should treat according to the medical condition, and if the subject's injury exceeds the treatment capabilities of the research department, consultation and assistance from relevant departments should be sought.
- Outpatients

Upon learning of an AE in a subject, the research physician should thoroughly inquire about the subject's symptoms, signs, and location at the time of the event and provide necessary explanations and guidance. An initial assessment of the severity and relevance of the AE should be made. If the subject is at a local medical institution, the physician should contact the attending doctor by phone to re-assess the severity of the AE and provide handling advice:

- General AE: Initial treatment at a local hospital may be advised, with a notification to closely monitor the outcome of the event;
- Significant AE: It is suggested that the subject return to the hospital for treatment or seek treatment at a local hospital, and promptly inform the principal investigator. If the local hospital's facilities are limited, a doctor should be sent for treatment. If necessary, log in to the Interactive Web Response System (IWRS) to initiate the unblinding procedure. Treatment suspension, medication dosage adjustment, and symptomatic treatment should be adopted as per the protocol requirements.

8.3.2 Recording of AEs

- The research physician should make detailed records of AE, which must include: the name of the AE, start and end times, severity, measures taken, relation to the research drug, and outcome.
- Detailed records of the occurrence, progression, and treatment of SAEs should be made in the original medical records as much as possible and entered into the eCRF forms. This SAE should be tracked until it is resolved properly, the condition stabilizes, or the cause is clearly identified.

**8.4 Severity grading of AEs**

Mild: Minor self-perceived symptoms that are tolerable, do not affect daily activities, are transient, resolve on their own during continued medication use, and require no treatment.

Moderate: Symptoms are noticeable, affect the subject's daily activities, persist for a longer duration, and may resolve on their own or after symptomatic treatment. They may interfere with the use of the study medication, possibly necessitating a reduction in dosage or discontinuation of the drug.

Severe: The subject’s bodily functions are impaired, losing the ability to work or live normally, with symptoms persisting for a long duration, requiring discontinuation of the medication and appropriate management before resolution.

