**Trial Schedule**

|  | **Medication Period** | | **Follow-up**^§^  **(± 3 days)** | | |
| --- | --- | --- | --- | --- | --- |
| **Visit window** | Screening | Treatment Period  (14 days + 1 day) | Day  30 | Day  60 | Day  90 |
| **General Procedures** | | | | | |
| Informed consent | X |  |  |  |  |
| Medical history | X |  |  |  |  |
| General data | X |  |  |  |  |
| Acute phase treatment | X |  |  |  |  |
| Inclusion/ Exclusion criteria | X |  |  |  |  |
| Concomitant diseases and medications | X |  |  |  |  |
| **Screening Indicators** | | | | | |
| Pregnancy test  (for women of childbearing age) | X |  |  |  | X |
| CT or MRI | X^‡^ |  |  |  | X |
| **Safety** | | | | | |
| Vital signs | X | X |  |  | X |
| Laboratory tests^†^ | X^‡^ | X |  |  | X |
| 12-lead electrocardiogram | X^‡^ | X |  |  | X |
| **Efficacy** | | | | | |
| MMSE | X | X |  |  | X |
| GCS | X | X |  |  |  |
| GOS-E |  | X |  |  | X |
| MoCA | X | X |  |  | X |
| LOTCA | X | X |  |  | X |
| ADL-BI |  | X | X | X | X |
| **Other Tasks** | | | | | |
| Allocation of drug numbers | X |  |  |  |  |
| Dispensing experimental drugs | X |  |  |  |  |
| Retrieval of remaining drugs |  | X |  |  |  |
| Recording concomitant medications |  | X | X | X | X |
| Adverse event recording |  | X | X | X | X |
| Efficacy assessment |  | X |  |  | X |
| Summary of trial completion status |  |  |  |  | X |

Abbreviations: ADL-BI, Activities of Daily Life-the Barthel Index scale; CT, computed tomography; GCS, Glasgow Coma Scale; GOS-E, Glasgow Outcome Scale-Extended; LOTCA, Loewenstein Occupational Therapy Cognitive Assessment; MMSE, Mini-Mental State Examination; MoCA, Montreal Cognitive Assessment; MRI, magnetic resonance imaging.

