**5.6 Trial Period**

Screening period (-72h to 0h) + Treatment period (14+1 days) + Follow-up period of 90 Days.

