**5.12 Treatment Period (14 days + 1 day)**

Prescriptions or medical orders are issued by research physicians based on randomly assigned drug numbers. Drug administrators dispense medications to research nurses based on these prescriptions or medical orders. Upon retrieval of the medication, the research nurse administers the prescribed dosages to the participants on a daily basis, with the regimen spanning a continuous period of 14 days. Within the 1-day window following the end of this administration period, the following tasks must be completed and recorded:

- Conduct vital signs checks.
- Researchers document changes in condition, AEs, concurrent illnesses, and concomitant medication use during the medication period.
- Participants to complete the MMSE, GCS, MoCA, LOTCA, GOS-E, and the ADL-BI for evaluation.

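### The Mild and Severe adverse event grades each contain a condition that can be met only on study drug, although every event must be graded up to 90 days after a 14-day course

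*Protocol*

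**What the plan says.** Section 8.4 sets three grades. Each opens with symptoms and function and then adds an element about the medication.

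- Mild: tolerable and short-lived complaints that leave daily life intact, and which "resolve on their own during continued medication use, and require no treatment".
- Moderate: noticeable, longer-lasting symptoms that affect daily life. The medication element is only a possibility: "They may interfere with the use of the study medication, possibly necessitating a reduction in dosage or discontinuation of the drug".
- Severe: impaired bodily function, "losing the ability to work or live normally, with symptoms persisting for a long duration", and "requiring discontinuation of the medication and appropriate management before resolution".

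On timing, section 5.12 describes daily dosing "with the regimen spanning a continuous period of 14 days", and section 5.6 gives the whole course as "Screening period (-72h to 0h) + Treatment period (14+1 days) + Follow-up period of 90 Days". Section 5.13 counts the Day 30, 60 and 90 visits from the end of medication. The Trial Schedule row reads "Adverse event recording | | X | X | X | X", so events are collected in the treatment period and at all three later visits. The definition of an adverse event in section 8.1 covers occurrences after taking trial medication and sets no end at the last dose.

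Section 8.3.2 lists what must be recorded for each event. The list includes "severity, measures taken, relation to the research drug, and outcome".

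**The concern.** In the Mild and Severe definitions the medication element is joined to the rest as a further requirement. It is not offered as an alternative or an example. Once dosing has ended there is no study drug to continue or to discontinue, so neither requirement can be met. A severity is still mandatory, and section 8.4 gives no other rule for events that begin after the last dose.

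On drug there is a second difficulty. Part of the grade depends on what was done with the study drug, although section 8.3.2 treats severity and measures taken as two separate items.

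At stake is the meaning of the severity grade. Safety is one of the two primary objectives (section 2) and adverse events are a safety endpoint (section 7.2). The grade is assigned at the site when the event is recorded, and 74 centers are planned (section 3.1). If sites resolve the wording differently for late events, grades may not be comparable between centers, or between the on-drug and off-drug periods. A later analysis plan cannot fully undo that.

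**Working it through.** The protocol states no figure on this point, so there is none to reproduce. The check compares the grade definitions with the collection window.

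**1. Which medication elements are required?** Mild: required. Moderate: permissive, because it speaks only of what may happen. Severe: required.

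**2. Apply the definitions literally to an event that starts after the last dose.**

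| Event off drug | Mild | Moderate | Severe | Result |
|---|---|---|---|---|
| Slight, passing, daily life unaffected | Not met: no drug is being continued | Not met: daily life is unaffected and the event is not prolonged | Not met: no loss of function and no drug to stop | No grade |
| Noticeable, longer-lasting, daily life affected | Not met | Met | Not met | Moderate |
| Incapacitating, long-lasting, needs care | Not met | Can be met | Not met: no drug to stop | At most Moderate |

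The same problem reaches a slight event that begins late in treatment and outlasts the final dose, because it does not resolve while medication continues.

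**3. Apply them on drug.** An incapacitating event that did not require the study drug to be stopped, such as an unrelated injury, meets the functional part of Severe but not the medication part. Its grade is then decided by the action on the drug.

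**4. How long is the off-drug period?** Inputs: 14 treatment days (section 5.12) and 90 follow-up days (section 5.6).

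- Off-drug share = follow-up days / (treatment days + follow-up days) = 90 / (14 + 90) = 90 / 104 = 86.5%.
- Counting the extra day of the treatment window: 90 / (15 + 90) = 90 / 105 = 85.7%.

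These are shares of planned observation time. The protocol gives no timing of adverse events, so the share of events affected cannot be calculated.

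**The case against.** The strongest reply is that the medication wording is a trailing clause. Each grade opens with symptom and function criteria that already separate the three levels, and a sensible investigator would grade a late event on those alone. One could also read the Severe clause hypothetically, as an event that would call for stopping the drug if it were still being given. The protocol provides for an eCRF filling guide with site training (section 9.3), medical review of the data (section 9.4) and protocol training (section 15.2). The guide is not available here and may settle the matter.

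This has force, and it limits the point in five ways.

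- A reader might infer that severity is defined wholly by what happens to the study drug. It is not: the medication condition is one element of Mild and Severe and optional in Moderate.
- A reader might infer that all off-drug events drift to Moderate. The text does not support that: a slight, passing event fails Moderate too and is left with no grade.
- A reader might take 86.5% as the proportion of events misgraded. It is a share of days, and events may cluster during treatment.
- A reader might fear that serious events are missed. The definition in section 8.1 does not use these grades, and the handling categories in section 8.3.1 are general, significant and serious.
- A reader might suspect bias between arms. The wording applies alike to all three blinded arms, and nothing in the document shows a differential effect. Nor does section 14 specify an analysis by severity, so no particular table can be said to be wrong.

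What the reply does not remove is the text itself. Setting the medication clause aside for late events, or reading it hypothetically, is sensible but is not written in the protocol. It asks each site to depart from the stated definition on its own judgement.

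**Conclusion.** The point holds as a defect of definition. Followed as written, section 8.4 cannot grade an off-drug event as Mild or Severe. An incapacitating event is capped at Moderate, a slight one has no grade, and on drug the grade is mixed with the action taken. This applies throughout the 90 days after dosing, out of 104 planned days.

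The conclusion rests on reading the medication clauses as joint requirements, which is their plain grammatical sense, and on no other protocol section supplying a rule for late events; none was found. The practical effect is inconsistent grading of late events. Its extent is unknown, because neither event timing nor the eCRF guide is available. No efficacy result, sample size figure or serious adverse event rule depends on it. It merits correction because the grade is a required safety item and the change is small.

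**What to change.** Reconcile section 8.4 with the Trial Schedule and section 8.3.2. State that the severity grade rests on the symptom and function wording already in section 8.4 and applies in the same way on and off drug. Take the medication element out of the grade definitions, and record any action on study drug only under the measures-taken item that section 8.3.2 already requires.

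This concerns how an event is classified. It leaves every rule on dosing, stopping treatment and event management as it stands in sections 4.3, 8.3.1 and 8.7.

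The cost is three edited sentences and a matching line in the eCRF guide. The stated trial period began in September 2019, so events may already have been graded. Any that began or continued after the last dose should be checked against the clarified wording, without knowledge of treatment allocation. No new data item is needed.
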